### 8.3 Data Safety Management Board (DSMB)

The DSMB will be composed of five individuals, one of whom will be the chairperson.

- The DSMB will first convene after the first 100 patients
- Subsequently, the DSMB will attend videoconferences every six months
- All adverse events will be reported to the DSMB for review. All serious events will be reported within 24 hours after being received by the coordinating center. Non-serious events will be reported within one week of reception by the coordinating center (Appendix V)
- All unexpected study-related or possibly study-related adverse events will be reported to the DSMB. Adverse events include but are not limited to unexpected death, inadvertent extubation, development of hemodynamic compromise during a recruitment maneuver or PEEP adjustment, sudden hypoxemia, hypercarbia or a pneumothorax during changes in ventilator setting in either the control or treatment group (Appendix V)
- The DSMB will monitor the overall status of the trial: number of patients enrolled overall and per each center, adherence to protocol overall and per center and results of the interim analysis.
- The DSMB include any of the following individuals:
  - Prof. [name], Outcomes Research/ P77 Cleveland Clinic [name] Cleveland, OH, USA, (chair)
  - Prof. [name], Massachusetts General Hospital, Boston, MA, USA
  - Prof. [name], University of Liverpool, Liverpool, UK
  - Prof. [name], University Erasme, Brussels, Belgium
  - Prof. [name], University Hospital of Bonn, Germany

## **9. ETHICAL CONSIDERATIONS**

### **9.1 Regulation statement**

This study will be conducted in accordance to the principles of the Declaration of Helsinki.

## **10. ADMINISTRATIVE ASPECTS AND PUBLICATION**

### **10.1 Handling and storage of data and documents**

All enrolled patients will receive a random patient identification code. The codebook will be stored digitally, encrypted with a double password, and as a hard copy under lock and key. All data will be stored for the length of the study and afterwards as required by local law or for further publication. All handling of personal data will comply with local law.

## 12. APPENDICES

### APPENDIX i.

| Table: Risk for PPC of Variables Selected for the Logistic Regression Model |                         |                         |                      |             |
|-----------------------------------------------------------------------------|-------------------------|-------------------------|----------------------|-------------|
|                                                                             | Bivariate Analysis      | Multivariate Analysis*  | $\beta$ Coefficients | Risk Score§ |
|                                                                             | OR (95% CI)
n = 1627 | OR (95% CI)
N = 1624 |                      |             |
| Age (yr)                                                                    |                         |                         |                      |             |
| ≤ 50                                                                        | 1                       | 1                       |                      |             |
| 51 – 80                                                                     | 3.1 (1.5 – 6.7)         | 1.4 (0.6 - 3.3)         | 0.331                | 3           |
| > 80                                                                        | 8.8 (3.8 – 20.3)        | 5.1 (1.9 - 13.3)        | 1.619                | 16          |
| Preoperative SpO 2 , %                                           |                         |                         |                      |             |
| ≥ 96                                                                        | 1                       | 1                       |                      |             |
| 91 – 95                                                                     | 3.1 (1.8 - 5.3)         | 2.2 (1.2 - 4.2)         | 0.802                | 8           |
| ≤ 90                                                                        | 15.2 (7.2 – 32.5)       | 10.7 (4.1 - 28.1)       | 2.375                | 24          |
| Respiratory infection in the last month                                     | 6.1 (3.4- 11.1)         | 5.5 (2.6 - 11.5)        | 1.698                | 17          |
| Preoperative anemia (≤ 10 g/dL.)                                            | 4.4 (2.4 – 8.01)        | 3.0 (1.4 - 6.5)         | 1.105                | 11          |
| Surgical incision                                                           |                         |                         |                      |             |
| Peripheral                                                                  | 1                       | 1                       |                      |             |
| Upper abdominal                                                             | 6.9 (4.0 – 11.9)        | 4.4 (2.3 - 8.5)         | 1.480                | 15          |
| Intrathoracic                                                               | 16.9 (8.4 - 34.1)       | 11.4 (4.9 - 26.0)       | 2.431                | 24          |
| Duration of surgery, h                                                      |                         |                         |                      |             |
| ≤ 2                                                                         | 1                       | 1                       |                      |             |
| > 2 to 3                                                                    | 6.1 (3.2 – 11.3)        | 4.9 (2.4 - 10.1)        | 1.593                | 16          |
| > 3                                                                         | 11.2 (6.3 – 20.1)       | 9.7 (4.7 - 19.9)        | 2.268                | 23          |
| Emergency procedure                                                         | 2.1 (1.2 - 3.7)         | 2.2 (1.04 - 4.5)        | 0.768                | 8           |

Abbreviations: CI, confidence interval; OR, odds ratio; SpO2, oxyhemoglobin saturation by pulse

High or intermediate risk for postoperative pulmonary complications following surgery:  
ARISCAT risk score ≥ 26

## **APPENDIX ii.**

### **Cumulated Ambulation Score (CAS)**

The patient is assessed on the following functions:

- . Transfer from supine-to-sitting-to-supine
- . Transfer from sitting-to-standing-to-sitting (from armchair)
- . Walking (with appropriate walking aid)

Each function is scored as follows:

- . Able to perform function independently – 2
- . Only able to perform function with assistance from one or two people – 1
- . Unable to perform function despite assistance from two people – 0

The CAS is calculated as the sum of values on a given day.

## APPENDIX iii.

### DEFINITIONS of pulmonary post–operative complications

- Aspiration pneumonitis:  
Defined as respiratory failure after the inhalation of regurgitated gastric contents
- Bronchospasm:  
Defined as newly detected expiratory wheezing treated with bronchodilators
- Mild respiratory failure:  
PaO2 < 60 mmHg or SpO2 < 90% in room air during at least 10 min air but responding to supplemental oxygen (excluding hypoventilation)
- Moderate respiratory failure:  
PaO2 < 60 mmHg or SpO2 < 90% despite supplemental oxygen (excluding hypoventilation)
- Severe respiratory failure:  
Need for non–invasive or invasive mechanical ventilation (excluding hypoventilation)
- ARDS:  
Mild, moderate or severe according to the Berlin definition:
- Pulmonary infection:  
Defined as new or progressive radiographic infiltrate plus at least two of the following: antibiotic treatment, tympanic temperature > 38°C, leukocytosis or leucopenia (WBC count < 4,000cells/mm^3 or > 12,000cells/mm^3) and/or purulent secretions
- Atelectasis:  
Suggested by lung opacification with shift of the mediastinum, hilum, or hemidiaphragm towards the affected area, and compensatory overinflation in the adjacent nonatelectatic lung
- Cardiopulmonary edema:  
Defined as clinical signs of congestion, including dyspnea, edema, rales and jugular venous distention, with the chest X–ray demonstrating increase in vascular markings and diffuse alveolar interstitial infiltrates
- Pleural effusion:  
Chest X–ray demonstrating blunting of the costophrenic angle, loss of the sharp silhouette of the ipsilateral hemidiaphragm in upright position, evidence of displacement of adjacent anatomical structures, or (in supine position) a hazy opacity in one hemithorax with preserved vascular shadows
- Pneumothorax:  
Defined as air in the pleural space with no vascular bed surrounding the visceral pleura
- New pulmonary infiltrates:  
Chest X–ray demonstrating new monolateral or bilateral infiltrate without other clinical signs

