#### 6.4 Sample size calculation

**Initial** sample size calculation was based on our primary hypothesis and primary study outcome, and was informed by data collected during a multicenter Spanish trial (ARISCAT) (see APPENDIX i) and a single-center, relatively small study reporting the effects of intraoperative higher PEEP and recruitment maneuvers on the incidence of postoperative desaturation, chest infection and bronchospasm in obese patients who underwent laparoscopic bariatric surgery.

These calculations indicated that 356 patients were required per group, assuming a two-sided significance level of 0.05 and a power of 80%, to detect the expected difference in postoperative pulmonary complications between the higher PEEP group of 30% and the lower PEEP group of 40% (risk ratio of 0.75). Assuming a dropout rate of 5%, **a total of 748 patients** (n=374 per group) were planned to be included into the study.

Sample size was re-estimated based on recommendations of the DSMB after data on the first 618 patients revealed that the incidence of the collapsed composite outcome was considerably lower than expected. In the revised calculations, the control group incidence was assumed to be 0.20 (instead of 0.40), and sample size was calculated to have 80% power at the overall 0.05 significance level to detect a relative risk (as originally planned) of 0.75. This design requires a maximum of 1912 patients, adjusting for the interim monitoring for efficacy and futility as described in section 8.2. Assuming a dropout rate of 5%, a total of 2013 patients need to be included into the study. East 6.0 interim monitoring software (Cytel, Cambridge, MA, USA) was used.

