### *Post-operative variables*

The patients will be assessed daily between the first and the fifth day after surgery as well as on the last day before discharge from hospital. Clinical data and the presence of pulmonary and extra-pulmonary postoperative complications will be scored, the date of development of any complication documented (for definitions, see APPENDIX iii.).

The documentation will adhere to the timetable in APPENDIX iv.

- Continuation of non-invasive or invasive mechanical ventilation outside of the operation room directly after surgery; if yes: specify indication and duration, hours
- Any new requirement of non-invasive CPAP or NPPV; if yes: specify indication, duration and intensity
- Any new requirement of invasive mechanical ventilation; if yes: specify indication, duration and intensity
- ICU stay directly postoperative; if yes: specify reason

- Any new admission or readmission to the ICU at any time in the post–operative period; if yes: specify reason
- Postoperative nausea and vomiting (PONV)
- Physiotherapy and breathing exercises
- CAS  to evaluate mobility, see Appendix ii
- Wound healing: impaired wound healing can be defined as an interruption in the timely and predictable recovery of mechanical integrity in the injured tissue
- Surgical wound infection; if yes: specify location (superficial *or* deep, abscess, empyema *or* phlegmon )
- Return of bowel function
- Any need for anti–arrhythmic and vasoactive medication; if yes: specify
- Post–operative fluid requirements (crystalloids, artificial colloids, or albumin; specify type and amount since last assessment)
- Post–operative transfusion of packed red blood cells, fresh frozen plasma , plasma frozen within 24 hours (FP24), fibrinogen, cryoprecipitate, PPSB and platelets in the preceding six hours; if yes: specify type and number of units transfused since last assessment
- Respiratory rate and peripheral oxygen saturation in room air, beach chair position
- Presence or absence of airway secretion (ask patient to cough and subjectively evaluate presence and consistency of sputum; if yes: purulent *or* not)
- Noninvasive mean arterial pressure
- Heart rate (bpm)
- Tympanic temperature; °C
- VAS evaluation for dyspnea, thoracic and abdominal rest and incident pain
- Chest X–ray – not mandatory
- Bedside spirometry (FVC, FEV1) – not mandatory
- BUN, Creatinine, AST, ALT, Bilirubin, Hb, Platelets, PT, PTT, white blood cell count

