### 8.2 Analysis

The primary endpoint is a collapsed composite of postoperative pulmonary complications occurring in the first five days after surgery. These complications include aspiration pneumonitis, bronchospasm, mild respiratory failure, moderate respiratory failure, severe respiratory failure, development of acute respiratory distress syndrome, pulmonary infection, atelectasis, pulmonary edema caused by cardiac failure, pleural effusion, pneumothorax and new pulmonary infiltrates (for definition, see Appendix iii). Patients who develop a least one of the above mentioned complications are considered as meeting the primary endpoint.

Interim analyses for efficacy and futility will be conducted at 50% (N=956), 75% (N=1434) and 100% (N=1912) of the planned enrollment, as needed, using a non-binding group sequential design with gamma spending functions ( $\gamma = -4$  for each of  $\alpha$  and  $\beta$ ). The table below shows the  $\alpha$  and  $\beta$  spent over the trial, z-statistic boundaries for efficacy and futility, and boundary crossing probabilities under the alternative hypothesis ( $H_1$ ). The corresponding P-value boundaries for efficacy (futility in parentheses) at the 1st, 2nd and final looks, respectively, are  $P \leq 0.006$  ( $P > 0.82$ ),  $P \leq 0.015$  ( $P > 0.35$ ) and  $P \leq 0.044$  ( $P > 0.044$ ). The Figure below displays the z-statistic boundaries for efficacy/harm and futility as a function of accrued sample size.

| Table: Z-statistic boundaries and boundary crossing probabilities (under $H_1$ );
Power=0.80, $\alpha=0.05$ , gamma spending functions ( $\gamma = -4$ ), $p_1=.20$ , $p_2=0.15$ |                      |      |                        |                 |              |             |                                             |          |
|-------------------------------------------------------------------------------------------------------------------------------------------------------------------------------------|----------------------|------|------------------------|-----------------|--------------|-------------|---------------------------------------------|----------|

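### Appendix iii leaves a new infiltrate with only fever or only purulent secretions outside every infiltrate component of the primary composite, so scoring runs event, no event, event as signs increase.

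*Protocol*

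**What the plan says.** Section 8.2 defines the endpoint: "The primary endpoint is a collapsed composite of postoperative pulmonary complications occurring in the first five days after surgery". It lists twelve components, among them "pulmonary infection, atelectasis, pulmonary edema caused by cardiac failure, pleural effusion, pneumothorax and new pulmonary infiltrates (for definition, see Appendix iii"). One is enough: "Patients who develop a least one of the above mentioned complications are considered as meeting the primary endpoint". For the definitions it points to Appendix iii.

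Appendix iii defines the two infiltrate components as follows.

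- Pulmonary infection: "Defined as new or progressive radiographic infiltrate plus at least two of the following: antibiotic treatment, tympanic temperature > 38°C". The list goes on with leukocytosis or leucopenia and purulent secretions, so there are four criteria and two are required.
- New pulmonary infiltrates: "Chest X–ray demonstrating new monolateral or bilateral infiltrate without other clinical signs".

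Appendix iii does not say what a clinical sign is. Section 7.2.4 describes the postoperative film as "Chest X–ray – not mandatory". It lists the white cell count among the postoperative variables without such a label, but refers to the timetable in Appendix iv, where routine laboratory tests are marked facultative on every postoperative day. Under section 7.2.1, outcomes are scored at each site by an investigator blinded to the intraoperative intervention. Section 6.1 expects about 90 centers.

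**The concern.** The two definitions should meet: a new infiltrate that falls short of infection should belong to the lesser component. They do not meet. One requires no sign, the other requires two criteria, and nothing covers the case between.

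Both components belong to the only endpoint that the protocol calls confirmatory. An assessor who applies the text literally scores a filmed infiltrate with fever as no event, while the same film in a patient without fever is an event. An assessor who overlooks the no-signs condition scores both as events. At stake are the consistency of scoring across sites and the meaning of the composite, which should not lose an event because a sign is added.

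**Working it through.** **Inputs.** The any-one rule and the list of twelve components (section 8.2), the two definitions (Appendix iii) and the facultative status of laboratory tests (Appendix iv). The point disputes no figure in the plan.

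**Step 1: enumerate.** Take a patient with a new infiltrate and no other component. Each of the four infection criteria is present or absent, which gives 2^4 = 16 combinations: 1 + 4 + 6 + 4 + 1 for 0, 1, 2, 3 and 4 criteria. Infection is met with two or more. New pulmonary infiltrates is met if no clinical sign is present. Since that term is undefined, use two readings: wide (all four criteria are signs) and narrow (only fever and purulent secretions are signs).

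| Criteria present | Combinations | Scored as event, wide reading | Scored as event, narrow reading |
|---|---|---|---|
| 0 | 1 | 1 | 1 |
| 1 | 4 | 0 | 2 (antibiotics alone; white cell count alone) |
| 2 | 6 | 6 | 6 |
| 3 | 4 | 4 | 4 |
| 4 | 1 | 1 | 1 |

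Under either reading, fever alone and purulent secretions alone are not events, while no sign and two or more criteria are. Those 2 combinations are lost for certain. The other 2 single-criterion combinations depend on the reading. These are counts of combinations, not of patients.

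**Step 2: an undrawn white cell count.** Of the 6 pairs of criteria, 3 include an abnormal count. If the count is not drawn, each leaves one recorded criterion:

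- count plus fever leaves fever alone: in the gap;
- count plus purulent secretions leaves purulent secretions alone: in the gap;
- count plus antibiotics leaves antibiotics alone: in the gap only under the wide reading.

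The other 3 pairs are unaffected.

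**Step 3: signs outside the list.** The no-signs condition is not limited to the four infection criteria. Read literally, a new infiltrate with, for example, dyspnea or rales and fewer than two listed criteria also meets neither definition.

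**Step 4: look for text that closes the gap.** No other part of the protocol assigns the one-sign case to a component. The patient still counts if one of the other components is met, such as respiratory failure, bronchospasm, atelectasis, pleural effusion, edema or ARDS.

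**The case against.** The strongest reply is that the gap is narrow. Any of the other components rescues the patient, and only patients who had a film can fall in it at all. In ordinary usage antibiotic treatment and a blood count are not clinical signs, so the certain part is two single-sign cases. All of this stands and limits the size. It does not give those cases a class.

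Three stronger readings are tempting, and the documents support none of them.

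- **Loss of power.** A reader might subtract lost events from the planned rates. If, purely as an assumption, 5% or 10% of events were lost equally in both arms, 0.20 and 0.15 would become 0.19 and 0.1425, or 0.18 and 0.135. Simulated power of the three-look design at 1912 patients would then fall from 80.7% to about 78% or 75%. But no frequency supports 5% or 10%. Section 6.4 also says the control rate was reset to 0.20 after data on the first 618 patients. The change summaries record no change to the pulmonary definitions in Appendix iii, so 0.20 probably already reflects the present wording, and a further deduction would count the loss twice.
- **Sicker patients are missed.** A single fever or an abnormal white cell count is also a general criterion for systemic inflammation in Appendix iii. It need not mean worse lung disease. What is shown is non-monotone scoring in the number of signs, not in severity.
- **Bias between arms.** Scoring is blinded and randomization is balanced per center (section 7.2.1). Differences between centers in reading the phrase do not by themselves favor an arm.

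**Conclusion.** The point holds as a defect of definition in the primary endpoint. A new infiltrate with fever alone or purulent secretions alone belongs to neither infiltrate component and is scored event-free unless another component applies. Antibiotics alone or an abnormal white cell count alone is scored according to how the assessor reads an undefined term. An optional blood test can decide the class when the second criterion is fever or purulent secretions.

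The certain part rests only on the text and on counting fever and purulent secretions as clinical signs. The number of patients affected cannot be derived from the documents. No effect on power or on the treatment contrast is shown. The change is worth making because the endpoint is the confirmatory one and the repair is small.

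**What to change.** Reword the last pulmonary definition in Appendix iii along these lines: new pulmonary infiltrates means a new infiltrate on chest X-ray, on one or both sides, that does not meet the definition of pulmonary infection, ARDS or cardiopulmonary edema, irrespective of other clinical signs. Every new infiltrate on film then counts toward the composite, and neither the undefined term nor an undrawn white cell count can remove it.

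Apply the rule to all patients, blinded to arm, including those already entered where the film result was recorded. The case report form is not shown, so whether that result is available for every earlier case has to be checked.

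Costs: one sentence in Appendix iii and in the endpoint derivation, and re-derivation of some earlier cases. The change slightly broadens a component after the trial was re-sized, so the composite rate may rise a little above that seen in the first 618 patients. A sensitivity analysis under the present Appendix iii wording would show how much the change matters.

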## DEFINITIONS of extra–pulmonary post–operative complications

- Systemic inflammatory response syndrome (SIRS):
 

Presence of two or more of the following findings: Body temperature  $< 36^{\circ}\text{C}$  or  $> 38^{\circ}\text{C}$  – Heart rate  $> 90$  beats per minute – Respiratory rate  $> 20$  breaths per minute or, on blood gas, a  $\text{P}_a\text{CO}_2 < 32$  mmHg (4.3 kPa) – WBC count  $< 4,000$  cells/mm^3 or  $> 12,000$  cells/mm^3 or  $> 10\%$  band forms
- Sepsis:
 

SIRS in response to a confirmed infectious process; infection can be suspected or proven (by culture, stain, or polymerase chain reaction (PCR)), or a clinical syndrome pathognomonic for infection. Specific evidence for infection includes WBCs in normally sterile fluid (such as urine or cerebrospinal fluid (CSF), evidence of a perforated viscera (free air on abdominal x–ray or CT scan, signs of acute peritonitis), abnormal chest x–ray (CXR) consistent with pneumonia (with focal opacification), or petechiae, purpura, or purpura fulminans
- Severe sepsis:
 

Sepsis with organ dysfunction, hypoperfusion, or hypotension
- Septic shock:
 

Sepsis with refractory arterial hypotension or hypoperfusion abnormalities in spite of adequate fluid resuscitation; signs of systemic hypoperfusion may be either end-organ dysfunction or serum lactate greater than 4 mmol/dL. Other signs include oliguria and altered mental status. Patients are defined as having septic shock if they have sepsis plus hypotension after aggressive fluid resuscitation, typically upwards of 6 liters or 40 ml/kg of crystalloid
- Extra–pulmonary infection:
 

Wound infection + any other infection
- Coma:
 

Glasgow Coma Score  $\leq 8$  in the absence of therapeutic coma or sedation
- Acute myocardial infarction:
 

Detection of rise and/or fall of cardiac markers (preferably troponin) with at least one value above the 99th percentile of the upper reference limit, together with: symptoms of ischemia, ECG changes indicative of new ischemia, development of pathological Q-waves, or imaging evidence of new loss of viable myocardium or new regional wall motion abnormality Or: sudden unexpected cardiac death, involving cardiac arrest with symptoms suggestive of cardiac ischemia (but death occurring before the appearance of cardiac markers in blood)
- Acute renal failure:
 

Renal failure documented as follows: Risk: increased creatinine x1.5 or GFR decrease  $> 25\%$  or urine output (UO)  $< 0.5$  ml/kg/h x 6 hr – Injury: increased creatinine x2 or GFR decrease  $> 50\%$  or UO  $< 0.5$  ml/kg/h x 12 hr – Failure: increase creatinine x3 or GFR decrease  $> 75\%$  or UO  $< 0.3$  ml/kg/h x 24 hr or anuria x 12 hrs – Loss: persistent ARF = complete loss of kidney function  $> 4$  weeks

- Disseminated intravascular coagulation:
 

DIC score documented as follows: Platelet count < 50 (2 points), < 100 (1 point), or  $\geq 100$  (0 points) – D-dimer > 4  $\mu\text{g/ml}$  (2 points), > 0.39  $\mu\text{g/ml}$  (1 point) or  $\leq 0.39$   $\mu\text{g/ml}$  (0 points) – prothrombin time > 20.5 seconds (2 points), > 17.5 seconds (1 point) or  $\leq 17.5$  seconds (0 points); if  $\geq 5$  points: overt DIC
- Gastro-intestinal failure:
 

Gastro-intestinal bleeding

Gastro-intestinal failure (GIF) score documented as follows: 0 = normal gastrointestinal function; 1 = enteral feeding with under 50% of calculated needs or no feeding 3 days after abdominal surgery; 2 = food intolerance (FI) or intra-abdominal hypertension (IAH); 3 = FI and IAH; and 4 = abdominal compartment syndrome (ACS)
- Hepatic failure:
 

Hepatic failure during short term follow up (5 postoperative days) is considered as follows: Ratio of total bilirubin on postoperative day 5 to postoperative day 1 > 1,7 and ratio of international normalized ratio (INR) on postoperative day 5 to postoperative day 1 >1,0; during long term follow up (until postoperative day 90) at new presence of hepatic encephalopathy and coagulopathy (INR > 1,5) within 8 weeks after initial signs of liver injury (e.g. jaundice) without evidence for chronic liver disease

